### Sample size calculation

2.6

There are no data available on effect size and standard deviations specific for cognitive function of targeted patients, therefore power calculation remains speculative. For the value of *δ*, we assume that it should come out between 0.25 and 0.5, and we set it as 0.3. With formula *n*
_1_ = *n*
_2_ = 2 × [(*t*
_α/2_ + *t*
_β/2_) *S*/*δ*]^2^, setting *α* at 0.05 and *β* at 0.20 in a two‐tailed independent *t*‐test indicated that a minimum of 62 patients per group is needed (totally 124 participants).

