### Additional study parameters

2.9

The information on age, sex, nation, family history of psychiatric disorder, age of onset, time of BD diagnosis, education level, use of mood stabilizer in early stage, number of depressive and manic episodes, history of euthymia (yes/no), and premorbid adjustment ability will be collected.

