### Blinding and study group allocation

2.10

Subjects will be divided into AT or NT group according to whether they had a history of receiving systemic antidepressant treatment in early stage. The screening process will be finished by two senior psychiatrists, and then the following rating works will be handed over to other investigators, which could keep the latter investigators blind to the subjects’ group assignments.

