### Statistical analysis

2.19

The data obtained from questionnaires and basic information are expressed in “mean ± standard deviation” in the case of normal distributions and in median and quartile in the case of nonnormal distributions. The comparisons in scores of each scale between two groups will be made by Covariance Analysis; the Chi Square and Analysis of Variance (ANOVA) test will be used to test the consistency of match between groups for factors such as age, sex, MADRS scores, YMRS scores, PAS scores, use of mood stabilizers, age of onset, number of attacks, and so forth, and the factors with significantly different distributions between two groups will be used as covariates. Furthermore, the two groups of patients will be combined as a whole and then Multiple Linear Regression equations will be used to analyze the linear relationship between each factor and neurocognitive function. The test level is α = 0.05.

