
To increase the power of this study, we have some considerations as following. First, we will perform the PAS measurement to adjust the potential difference in premorbid function that may confound the cognitive performance of participants. Second, it is required that participants should have a euthymic state for 4 weeks at least before enrollment because the duration in euthymia is associated with the quality of life (Pascual‐Sánchez et al., 2019), which has been found associated to cognitive function (Sánchez‐Morla et al., 2009). Third, we have two separate groups of investigators before and after group assignment to keep the later investigators blind to the assignment and then to avoid subjective bias on assessment of scales. Lastly, we set the range of age between 18 and 50 years to decrease the influence of aging in cognitive performance.

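### Choosing ANCOVA covariates by whether they differ significantly between AT and NT can leave confounders of moderate size unadjusted in this non-randomised comparison

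*Protocol article*

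**What the plan says.** Section 2.10 forms the groups from treatment history: "Subjects will be divided into AT or NT group according to whether they had a history of receiving systemic antidepressant treatment". Section 2.19 compares scale scores by analysis of covariance. It first tests the two groups against each other on "age, sex, MADRS scores, YMRS scores, PAS scores, use of mood stabilizers, age of onset, number of attacks, and so forth", and then states that "the factors with significantly different distributions between two groups will be used as covariates". The only level given is "The test level is α = 0.05", with no separate level for the screening tests. No covariate is fixed in advance, and the candidate list is open-ended.

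The Discussion takes a different line on one of these factors: "we will perform the PAS measurement to adjust the potential difference in premorbid function that may confound the cognitive performance of participants". It attaches no condition to that adjustment.

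Section 2.9 shows that further background variables will be collected, among them "age of onset, time of BD diagnosis, education level, use of mood stabilizer in early stage", as well as family history of psychiatric disorder.

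**The concern.** A confounder biases the group difference by roughly its imbalance multiplied by its coefficient on the outcome. The rule in 2.19 looks only at whether the imbalance reaches p < 0.05. It can therefore go wrong in three ways.

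- A factor that is moderately imbalanced and strongly related to cognition is dropped whenever the screen misses it. A non-significant test at this sample size does not show balance.
- A strong predictor of cognition that happens to be balanced is also dropped, which gives away precision.
- A factor that lies on the path from antidepressants to cognition is admitted if it differs. Number of attacks is in the screened list, while the Background and Discussion describe antidepressants as possibly provoking manic or hypomanic episodes, which in turn may harm cognition. Adjusting for it could remove part of the effect under study.

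The final model also depends on the data, and the p-values and intervals take no account of the selection step. At stake is the main AT versus NT comparison of neurocognitive function.

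**Working it through.** **Inputs.** From the documents: 62 per group (2.6), screening level 0.05 (2.19), groups not randomised (2.10). The documents give no imbalance for any factor and no correlation with cognition, so those values are assumptions below.

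The plan's own figure of 62 cannot be reproduced from its stated inputs because S is not given. With δ = 0.3 in SD units, n = 2 × [(1.960 + 0.842)/0.3]² gives 175 per group; 62 needs S of about 0.60. Nothing below depends on this, since only the planned group size is used.

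**Step 1: what the screen can detect.** For a two-sided t-test with 122 degrees of freedom, the smallest observed difference that reaches significance is t(0.975; 122) × √(2/62) = 1.980 × 0.1796 = 0.356 SD. Anything smaller is never adjusted for. Power from the noncentral t distribution:

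| True imbalance | Power of screen | Left unadjusted |
|---|---|---|
| 0.2 SD | 20% | 80% |
| 0.3 SD | 38% | 62% |
| 0.4 SD | 60% | 40% |
| 0.5 SD | 79% | 21% |

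For a binary factor, 40% versus 55% is detected with about 39% power.

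**Step 2: residual bias with one confounder.** Take an imbalance of 0.3 SD and a correlation of 0.5. With no adjustment at all the bias is 0.3 × 0.5 = 0.15 SD. In simulation (40,000 studies, no true effect), the studies in which the screen missed the factor had an average bias of 0.094 SD. They made up about 62% of all studies, so the overall bias is 0.62 × 0.094 ≈ 0.06 SD, with 5.9% false positives. Always adjusting gave 0.00 SD and 5.1%.

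**Step 3: range of scenarios.** Simulated studies (6,000 to 8,000 per scenario), 62 per group, no true group effect, independent confounders, outcome with unit within-group SD:

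| Assumed confounders | Bias under 2.19 | False positives under 2.19 |
|---|---|---|
| One, 0.3 SD, coefficient 0.4 | 0.05 SD | 5.6% |
| Three, 0.3 SD, coefficient 0.4, one in the opposite direction | 0.05 SD | 5.6% |
| Three, 0.3 SD, coefficient 0.2 | 0.07 SD | 6.6% |
| Three, 0.3 SD, coefficient 0.3 | 0.105 SD | 8.8 to 9.4% |
| Three, 0.3 SD, coefficient 0.4 | 0.144 SD | 12.1 to 12.6% |

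Entering the same factors regardless of their p-values brought bias to about zero and false positives to about 5%.

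**Step 4: precision when the factors are balanced.** With a true d of 0.5 and three balanced predictors, the 2.19 rule gives about 80% power. Always adjusting gives about 83% with coefficients of 0.2 (R² = 3 × 0.2² = 0.12) and about 96% with coefficients of 0.4 (R² = 3 × 0.4² = 0.48).

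**Step 5: PAS.** Section 2.19 puts PAS among the screened factors, so it is left out whenever its test gives p ≥ 0.05. The Discussion presents adjustment for PAS as a feature of the design without that condition.

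**The case against.** The strongest reply has four parts.

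First, the design already limits confounding. Sections 2.4 and 2.5 restrict age to 18 to 50, require at least four weeks of euthymia, and exclude psychotic symptoms, ADHD, substance abuse, neurological disease, IQ below 70 and recent use of drugs that affect cognition. This stands. A reader might infer that the covariate rule is the only protection against confounding; it is not. It is the only stated statistical adjustment of the AT versus NT comparison. The pooled multiple regression in 2.19 does not change that, because it is described as relating each factor to cognition and is not said to include group.

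Second, the PAS passages can be read together, as adjusting if a difference is found. A reader might call them a flat contradiction, but the documents do not support that. They are inconsistent, because the Discussion states no significance condition and 2.19 imposes one.

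Third, the size of the harm rests on chosen inputs. This stands too. A reader might quote a false-positive rate above 12% as the consequence of the plan. That figure belongs to the severe end, with three independent confounders all pushing the same way and together explaining 48% of the variance. With one confounder, or with partly cancelling ones, inflation is small, although bias of about 0.05 SD remains.

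Fourth, the Background calls the study mainly explorative. That lowers the stakes but does not justify a rule that discards confounders, particularly when the stated hypothesis is directional.

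A reader might also infer from 2.9 that medication at the time of testing goes unrecorded. That is a separate data-collection question that a condensed article may leave to the full protocol, and it is no part of this point.

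**Conclusion.** The point holds. The rule is written into the current text, so it is not a detail left to an analysis plan. Followed as written, it would leave a true 0.3 SD imbalance unadjusted about 62% of the time. Under the assumed scenarios the residual bias is about 0.05 to 0.145 SD, with about 5 to 13% false positives instead of 5%. Where in that range the study would fall depends on the number, direction and strength of the confounders, which the documents do not give. The screening power and the 0.36 SD threshold follow from the planned group size and the 0.05 level, for a continuous factor compared by a t-test or the equivalent two-group ANOVA. The inconsistency over PAS and the possible admission of number of attacks as a covariate follow from the text alone.

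**What to change.** In 2.19, replace the significance screen with a fixed set of pre-exposure covariates that are already collected: age, sex, education level, family history of psychiatric disorder, age of onset and PAS score. Enter them in the ANCOVA whatever their p-values. Report standardised differences to describe balance, in place of tests.

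Keep number of attacks and the interval from first depressive onset to bipolar diagnosis out of the main model, and use them only in sensitivity analyses. The first may lie on the causal path. The second is the exposure window itself and may be shortened if antidepressants bring on a switch, so it should not be treated as a pre-exposure factor. Align 2.19 with the Discussion so that both say PAS is always adjusted for.

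The cost is a change of wording before the data are examined and about six degrees of freedom out of 122 (124 patients less two group means). No new data are needed.

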## DISCUSSION

3

Regarding the critical role of cognitive impairment in psychosocial disability and poorer quality of life, improving cognitive function has become a crucial goal in the management of BD patients. In this regard, increasing amount of research examining pharmacological and psychotherapeutic treatments was performed during the past decade (Alda et al., 2017; Solé et al., 2015). The research outcomes are inconsistent and no therapeutic intervention with sufficient efficacy is well‐established for improving cognitive dysfunction of BD yet (Miskowiak et al., 2016), although some of psychotherapeutic treatments or drugs appear as promising candidates. Many factors contributed to the discrepant outcomes such as poor randomization procedure, age of onset, number of depressive and manic episodes, severity of symptoms, and medications used specifically. In view of significantly delayed diagnosis of BD and common use of antidepressants in early stage, the effect of antidepressant agents on cognitive function has attracted increasing attention. But the data are still relatively rare, and the evidence is controversial. For example, a meta‐analysis estimated the relationship between antidepressant use and cognitive impairment and found that the odds of cognitive impairment were positively associated with antidepressant use in participants with an average age equal to or more than 65 years (odds ratio [OR] = 1.65), whereas those with participants aged less than 65 revealed an even stronger association (OR = 3.25) (Moraros et al., 2017); and also the study by Leng and colleagues illustrated that users of selective serotonin reuptake inhibitors and trazodone were as more as two to three times to develop dementia compared with the nonusers 5 years later, although the use of tricyclic antidepressants or other antidepressants was not involved in cognitive impairment (Leng et al., 2018). The evidence above suggests that antidepressant use could be a contributor for cognitive impairment of patients with mood disorder. Importantly, it is believed empirically that antidepressant treatment could deprave the natural course of BD and switch from depressive episode to episode of mania, hypomania, or mixed state (Viktorin et al., 2014), which may undermine the cognitive performance of bipolar patients (Goodwin et al., 2008). For instance, it was found that the higher number of manic and/or hypomanic episodes was negatively correlated with the cognitive performance of euthymic BD patients (*n* = 99) such as NCI, visual memory, and working memory in a 5‐year follow‐up longitudinal study (Sánchez‐Morla et al., 2019); furthermore, BD patients (*n* = 33), especially those with multiple mood episodes including mania, hypomania, and/or mixed state, showed severe impairments in emotional memory than healthy controls (*n* = 20) (Fijtman et al., 2020). Considering the significantly delayed diagnosis of BD and common use of antidepressants in clinical practice, such potential scathing effects should gather more attention. In contrast, another meta‐analysis suggested that antidepressants played a significant positive role in promoting psychomotor speed and delayed recall, with no significant difference between diverse types of antidepressants (Rosenblat et al., 2015). This is in line with the evidence from preclinical research that antidepressant agents could promote executive function and environmental information processing through integrating newborn neural cells into the hippocampal dentate gyrus (Tunc‐Ozcan et al., 2019). However, these data rarely came from clinical trial specifically focusing on the use of antidepressants in bipolar patients in early stage. To this end, the current study aims to clarify this issue by examining the cognitive function between bipolar patients who initiated with depressive episode and being with and without systemic antidepressant treatments in early stage. Additionally, the contemporary management of disease not only requires symptomatic relief but also pursues functional rehabilitation. Therefore, we will also examine the effect of antidepressant treatments in early stage on global function and quality of life of participants because both aspects are highly associated with cognitive function. Considering the potential influence of antidepressant use on progressing of course, the information on sleep quality and positive and negative affect will also be collected. Finally, the peripheral level of NSE will be tested to explore the potential biological mechanism of cognitive impairment.

To increase the power of this study, we have some considerations as following. First, we will perform the PAS measurement to adjust the potential difference in premorbid function that may confound the cognitive performance of participants. Second, it is required that participants should have a euthymic state for 4 weeks at least before enrollment because the duration in euthymia is associated with the quality of life (Pascual‐Sánchez et al., 2019), which has been found associated to cognitive function (Sánchez‐Morla et al., 2009). Third, we have two separate groups of investigators before and after group assignment to keep the later investigators blind to the assignment and then to avoid subjective bias on assessment of scales. Lastly, we set the range of age between 18 and 50 years to decrease the influence of aging in cognitive performance.

### Limitations

3.1

There are some limitations of the current study. First, some information, such as history of antidepressant treatment and first manic/hypomanic episode, is mainly derived from patients’ memory, which may lead to a recall bias. For another, we assume a systemic antidepressant treatment as a consecutive therapy with adequate dosage of antidepressants for 6 weeks at least, but regardless of the antidepressant types and dose differences, which may obscure the potential effect of specific type or dose of drug. Finally, there are no data available on standard deviations and effect size for neurocognitive function of targeted patients, therefore the putative sample size might increase the risk of type II error.

## CONCLUSION

4

In summary, despite these limitations, the present study is expected to help us look further into the effect of antidepressant use in early stage on the cognitive function of patient with BD and may provide clues for inspecting the pathophysiological association/discrepancy between unipolar depression and bipolar depression.

### PEER REVIEW

The peer review history for this article is available at https://publons.com/publon/10.1002/brb3.2360.

## Data Availability

The related data and materials are available from the corresponding author on reasonable request.
